### Protocol description

Volunteers who meet the inclusion criteria will be given an information sheet and asked to provide written consent to participate in the trial. They will then undergo a physical examination screening for the presence of other contra-indications to thoracic MB or MT such as thoracic spine surgery or recent trauma followed by an information session designed to familiarise them with the use of a treadmill. After a volunteer has successfully completed these tasks, baseline measurements will be taken. These include age, height, weight, blood pressure, heart rate, lung function assessment (spirometry), chest wall expansion (tape measure) and quality of life scores (SF-36). A participant is then enrolled in the trial, given a trial-specific identification (ID) number and allocated to a group on a sequential basis using a computer-generated random sequence list drawn up prior to the start of the trial by a person not involved in any other aspect of the trial. Participants will be directed to not reveal their group allocation to the blinded assessor during assessment. The study protocol flow of participants is outlined in Fig. 1.

**Fig. 1 Fig1:**
[figure not shown]
Flow of participants through the trial. *Ex* exercise, *MB* mobilisation, *MT* manipulation

All outcome measures will be taken by an assessor who is blinded to a participant’s group allocation. Lung function measurements (spirometry) will be measured in the standing position and include FEV_1_ and FVC. The initial treadmill walking speed will have been determined at the information session conducted in conjunction with the physical screening examination. This speed is set at a participant’s ‘comfortable walking pace’ as agreed to at that screening session. The SPIRIT figure showing the respective time points for enrolment, interventions and assessments is provided as Fig. 2.

**Fig. 2 Fig2:**
[figure not shown]
SPIRIT figure showing times points for enrolment, interventions and assessments. *Ex* exercise, *MB* mobilisation, *MT* manipulation, *FEV*_*1*_ forced expiratory volume in the 1st second, *FVC* forced vital capacity, *SF-36* 36-Item Short Form Health Survey

All MB and MT will be administered by students enrolled in the Masters of Osteopathic Medicine program at Southern Cross University who have been trained in the relevant manual therapy techniques used in this trial. They will be under supervision at all times by a registered osteopath.

A manipulation will be deemed successful by the presence of an audible release. All releases will be recorded on the participant’s file by the treating intern as either ‘absent’ (0), ‘single’ (1), or ‘multiple’ (2) for each manipulation. Should a deviation from the intervention protocol occur, the supervisor will be on hand to either approve the deviation or ensure a return to protocol. Any protocol violations, whether for clinical or non-clinical reasons, will be recorded on the participant’s file by the treating intern at each intervention session.

### Sample size calculation

Sample size calculation was based on change in FVC and the ability to detect a difference in lung function from baseline. The minimum clinically important difference (MCID) for FVC is 200 ml with a standard deviation of 48 ml obtained from previous studies on people with and without a history of respiratory disease [9, 16, 17]. With a power of 0.8 (80%), an alpha of 0.05 and an MCID for FVC of 200 ml, the minimum sample size per group was calculated to be 112. Assuming a drop-out rate of 10%, the minimum cohort size required is 372 (three groups of 124).

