**Discussion:**

This randomised controlled trial is designed to investigate whether manual therapy can mitigate the effects of age-related changes in lung function and whether there is a difference in effect between different forms of manual therapy. This is the first fully powered trial designed to test this hypothesis on healthy males and females in this age range.

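### The printed sample size inputs (200 ml, SD 48 ml, alpha 0.05, power 0.8) give about 3 per group, not 112, so the stated 80% power cannot be verified

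*Protocol article*

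**What the plan says.** The Sample size calculation section sizes the trial on change in FVC and on "the ability to detect a difference in lung function from baseline". Its inputs are:

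- **Difference and SD:** "The minimum clinically important difference (MCID) for FVC is 200 ml with a standard deviation of 48 ml". The figures are attributed to previous studies in people with and without respiratory disease.
- **Error rates:** "With a power of 0.8 (80%), an alpha of 0.05 and an MCID for FVC of 200 ml". Sidedness is not given.
- **Result:** "the minimum sample size per group was calculated to be 112", raised to 124 per group (372 in total) for 10% drop-out.

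No other SD, correlation, contrast or multiplicity adjustment is given. The Statistical analysis section plans a between-group ANCOVA with baseline as covariate and a significance threshold of 0.05. The aims, at the end of the Background, are whether manual therapy has an effect and whether its two forms differ.

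The discussion paragraph of the Abstract concludes: "This is the first fully powered trial designed to test this hypothesis on healthy males and females in this age range". The Background and the main Discussion also call the trial fully powered.

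**The concern.** An SD of 48 ml is less than a quarter of the 200 ml difference. Effects that large relative to their spread need only a handful of participants, so a result of 112 per group cannot follow from these inputs. At least one printed input, or the calculation itself, is not what it appears to be.

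This paragraph is the only justification given for the sample size, and FVC is a primary outcome. If the SD is wrong as printed, a reader does not know what difference the trial can detect or with what power. The statements that the trial is fully powered rest on the same paragraph, as does the contrast the Discussion draws with an earlier study that it says was not adequately powered.

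**Working it through.** **Inputs (Sample size calculation section).** Difference 200 ml, SD 48 ml, alpha 0.05, power 0.8, three equal groups, stated result 112 per group. A two-sided test is assumed first, because sidedness is not stated.

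**1. Attempt to reproduce 112.** The standardised effect is 200/48 = 4.17.

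Normal approximation, two groups: n = 2 × (1.960 + 0.842)² × (48/200)² = 0.90 per group. This formula is not reliable at so small a size, so exact power was calculated:

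| Calculation (SD 48 ml, 200 ml, two-sided 0.05) | Power at n = 2 | Power at n = 3 | n needed |
|---|---|---|---|
| Two-sample t-test | 0.59 | 0.96 | 3 per group |
| Paired (change from baseline, one group) | 0.36 | 0.93 | 3 |
| Three-group ANOVA, means 0/100/200 | 0.57 | 0.94 | 3 per group |
| Three-group ANOVA, means 0/0/200 | 0.69 | 0.98 | 3 per group |

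The arm means in the ANOVA rows are assumptions; the article gives none. One-sided testing and Bonferroni adjustment for up to six comparisons leave the requirement between 1 and 4. Adjusting for baseline, as the planned ANCOVA does, can only reduce the residual SD, so it does not help to reach 112. The stated figure is 112/3 ≈ 37 times the recomputed one.

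**2. Could the two figures have been swapped?** With a difference of 48 ml and an SD of 200 ml:

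- two-sample: 273 (two-sided) or 215 (one-sided) per group;
- paired: 139 (two-sided) or 109 (one-sided).

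Only the one-sided paired figure comes near 112. It reverses the stated roles of the two numbers and is not a between-group test.

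**3. What 112 per group would detect with SD 48 ml.** 48 × √(2/112) × (1.960 + 0.842) = 18.0 ml, and the exact t-test also gives 18.0 ml. That is 9% of the stated MCID.

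**4. The SD that 112 per group implies for 200 ml at 80% power.**

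- Two-sample, normal formula: 200 / [√(2/112) × 2.802] = 534 ml. The exact t-test gives 532 ml.
- Omnibus ANOVA, means 0/100/200: 480 ml.
- Omnibus ANOVA, means 0/0/200: 554 ml.

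The between-group readings at alpha 0.05 thus span roughly 480 to 550 ml, ten or more times the printed SD.

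**5. Two-sample power at 112 per group for 200 ml, two-sided 0.05, for assumed SDs.**

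| SD of FVC change (ml) | Power |
|---|---|
| 48 | effectively 1.00 |
| 400 | 0.96 |
| 480 | 0.87 |
| 532 | 0.80 |
| 550 | 0.77 |
| 600 | 0.70 |

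The answer depends on an SD that the article does not show.

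**The case against.** **The 112 may be right and only the SD misprinted.** This is the best defence. An SD of 480 ml gives 112 per group (power 0.800) in a three-group ANOVA with evenly spaced means, so a slipped factor of ten is plausible. It remains one possibility. The fit depends on assumed means: with 0/0/200, an SD of 480 ml needs only 85 per group. An SD of 532 ml in a two-sample t-test fits 112 equally well. The article states neither an SD of that size nor an omnibus test.

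**The trial need not be underpowered.** This stands. A reader might infer that a much larger SD leaves the between-group comparisons short of power. For the stated 200 ml at the stated alpha of 0.05, pairwise power is 0.87 at SD 480 ml and 0.80 at SD 532 ml, and this applies to manipulation versus mobilisation as much as to either arm versus exercise. A claim of low power for that comparison needs a target below 200 ml or a stricter alpha. The article sets neither.

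**Nor does it show gross over-recruitment.** A reader could take 48 ml at face value and conclude that far too many people are being enrolled. That assumes the least secure figure in the paragraph is the correct one.

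**The reference to a difference from baseline is loose, not contradictory.** The Outcome measurements section defines the metric as mean change from baseline, and the analysis compares groups. The wording can be read as a between-group difference in change, though it should say so.

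None of this reconciles 48 ml with 112. Nor can the gap be put down to the brevity of a journal article: the inputs are printed, and they contradict the printed result.

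**Conclusion.** The point holds as an internal arithmetic contradiction. The printed inputs require about 3 per group against 112 stated, under every standard two-sample, paired or three-group ANOVA calculation that keeps 200 ml as the difference and 48 ml as the SD.

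What follows is limited. The 80% power for 200 ml, and the fully powered claim in the Abstract, Background and Discussion, cannot be verified from the article. They are not refuted. The implied SD of roughly 480 to 550 ml is a back-calculation that takes 112, 200 ml, 80% power and an unadjusted two-sided 0.05 as correct. It does not establish which figure was used. The size of the contradiction does not depend on that reconstruction.

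The paragraph must be corrected, because it is the sole basis for the sample size.

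**What to change.** Correct the Sample size calculation section from the original calculation, stating:

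- the SD of FVC change actually used, and which cited study or studies it comes from;
- the test (omnibus or pairwise), the between-group contrast powered, any assumed arm means, and the alpha with its sidedness;
- that the target is a between-group difference in change from baseline;
- the power that 112 per group gives for a 200 ml between-group difference, separately for manual therapy versus exercise and for manipulation versus mobilisation.

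If the confirmed SD does not give 80% for one of these contrasts, report the power it does give and limit the fully powered wording in the Abstract, Background and Discussion to the contrasts that reach it.

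The cost is one rewritten paragraph and possibly a few words elsewhere. The downside is that the stated power may become less favourable. Whether the sample size itself is adequate cannot be said until the SD is confirmed.

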### Statistical analysis

Data will be reported as group means, standard deviations and 95% confidence intervals. Analysis will be performed as an analysis of covariance (ANCOVA) for difference between groups with baseline as a covariate. Standard errors will be calculated using a non-parametric bootstrap to allow for the different error variances for each group. A *p* value of < 0.05 has been set for statistical significance. For outcomes found to be statistically significant, the proportion of participants with a change greater than the MCID will be calculated for each outcome. The number needed to treat will be calculated using Bender’s method for confidence intervals. Missing data will be accounted for by using an intention-to-treat analysis with data from subjects lost to follow-up imputed using the multiple imputation method.

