
Participants will be recruited through self-referral in response to public advertisements placed in the local printed media and articles broadcast on the radio and/or television calling for volunteers for the trial. For logistical reasons the trial will be conducted at two sites: Southern Cross University’s Health Clinic in Lismore and Southern Cross University’s Health Clinic in the Gold Coast. The two sites will run sequentially with enrolment at the Gold Coast site not commencing until completion of the trial at the Lismore site. The main reasons for conducting the trial in this manner are recruitment and quality assurance. As Lismore is a medium-sized town in rural New South Wales (population 27,000), it is unlikely that the Lismore site will be able to generate sufficient participants for full enrolment. Adding the Gold Coast site, with its higher proportion of people over the age of 50, will improve the possibility of full enrolment. As the two sites are located approximately 98 km apart, achieving an acceptable level of quality assurance with the resources available mandates that the two sites be run consecutively.

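### The stated ANCOVA adjusts for the baseline value only; a pre-specified site term, optionally with age, height and sex, would give a small and nearly free gain in precision

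*Protocol article*

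**What the plan says.** All references are to the protocol article.

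- **Model** (Statistical analysis): "Analysis will be performed as an analysis of covariance (ANCOVA) for difference between groups with baseline as a covariate". Baseline is the only covariate named. On precision: "Standard errors will be calculated using a non-parametric bootstrap to allow for the different error variances for each group". Resampling by site is not mentioned.
- **Sites** (Study design): "For logistical reasons the trial will be conducted at two sites", and "The two sites will run sequentially with enrolment at the Gold Coast site not commencing until completion of the trial at the Lismore site".
- **Allocation** (Protocol description): participants are "allocated to a group on a sequential basis using a computer-generated random sequence list drawn up prior to the start of the trial". One list is described. Blocking and stratification are neither stated nor ruled out.
- **Baseline data** (Protocol description): "These include age, height, weight, blood pressure, heart rate, lung function assessment (spirometry" and further items. Sex is not in that list, although Participant characteristics admits both sexes.
- **Outcome metric** (Outcome measurements): mean change from baseline.

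**The concern.** Because the second site opens only when the first has finished, a single site indicator captures both place and period. If mean change in FVC or FEV1 differs between Lismore and the Gold Coast for any reason, the stated model has no term to absorb it. Two things follow. The difference adds to residual variance, and if the arms happen to differ in their share of Lismore participants, part of it moves the arm contrast by chance. Age and height are collected anyway and may explain further variation in change, but the stated model does not use them.

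What is at stake is the precision of the three-arm comparison, including mobilisation against manipulation, which is one of the trial's aims. Validity is not at stake.

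**Working it through.** The article gives no figure for a site effect, for the split between sites, or for the variance that age and height explain after baseline. Those quantities are assumed below and shown as ranges.

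**1. The plan's own figure, as a scale for the SD.** Sample size calculation gives a difference of 200 ml, SD 48 ml, power 0.80, alpha 0.05 (taken as two-sided) and 112 per group. The two-group formula gives n = 2 × (1.960 + 0.842)² × (48/200)² = 0.90, that is 1 per group, so 112 is not reproduced. An n of 112 needs an SD of about 200 × √(112 / (2 × 7.849)) = 534 ml. That discrepancy is a separate matter. Here it means only that the residual SD in ml is uncertain between about 48 and 534, so site effects are expressed in residual SD units.

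**2. Cost of leaving site out of the residual.** Let d be the site effect in residual SD and p the share of participants at the first site. Omitting site multiplies the residual SD, and so the reported SE, by √(1 + p(1 − p)d²). For p = 0.5 and d = 0.5 this is √1.0625 = 1.031.

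| d | p = 25% | p = 33% | p = 50% |
|---|---|---|---|
| 0.1 | +0.09% | +0.11% | +0.12% |
| 0.3 | +0.84% | +1.0% | +1.12% |
| 0.5 | +2.32% | +2.74% | +3.08% |

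In ml, 0.1 to 0.5 SD is 4.8 to 24 ml if the SD is 48, and 53 to 267 ml if it is 534. An assumed 100 ml site difference with p = 0.5 would give √(48² + 0.25 × 100²) = 69 ml, which is 44% above 48 (power for 200 ml would still be about 100%). Against 534 ml it adds about 0.4%.

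**3. Chance imbalance in site mix.** With an unrestricted list, 124 per arm and p = 0.5, the SD of the difference in site share between two arms is √(0.25 × 2/124) = 0.0635. The 95% range is ±1.96 × 0.0635 = ±12.4 points. An assumed site difference in change of 25, 50 or 100 ml then shifts a contrast by up to about 3.1, 6.2 or 12.4 ml. The last is 6% of 200 ml. In 10,000 simulated lists of 372 with p from 25% to 50%:

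- simple or unblocked list: SD 5.4 to 6.4 points, 95th percentile of the absolute difference 10.5 to 12.4 points;
- one list in blocks of six: 95th percentile at most about 1.6 points.

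**4. Validity.** Each scenario used 8,000 simulated trials with 112 per arm, a site effect of 0, 0.3 or 0.5 SD, a height-like covariate (correlation 0.7 with baseline, partial R² 0 or 0.05), and a blocked or unblocked list. Model-based standard errors were used, not the planned bootstrap. With baseline as the only covariate:

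- mean error was at most 0.004 SD;
- where a real effect was omitted, type I error was 4.1% to 5.3%;
- in the worst unblocked case (site 0.5 SD, partial R² 0.05), the SD of the estimate was 0.142 against 0.136 when adjusted, about 5%;
- with a blocked list and a 0.5 SD site effect alone, the SD of the estimate did not change (0.134 both ways). Omitting site only made the test slightly conservative (4.4% against 5.0%).

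**5. Extra covariates.** A partial R² of r beyond baseline multiplies the SE by √(1 − r).

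| Partial R² (assumed) | SE falls by | Power at 112 per group if 80% without it |
|---|---|---|
| 0.01 | 0.5% | 80.4% |
| 0.05 | 2.5% | 82.0% |
| 0.10 | 5.1% | 84.0% |
| 0.20 | 10.6% | 88.0% |

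**The case against.** The strongest reply is that nothing here is an error. ANCOVA on baseline is a valid analysis of a randomised comparison. The section is one condensed paragraph, and a full analysis plan may add covariates. This stands, and it limits the point to an improvement. It does not remove the point, because the paragraph does name a covariate set and site is not in it.

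A second reply is that, with sites run in sequence, an ordinary blocked list would balance the arms within each site almost as well as stratification. This also stands: the ±12 points apply only to an unblocked list. Under blocking, the site term still takes the site difference out of the reported SE.

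A third is that baseline FVC or FEV1 already carries much of what age and height contribute, so their gain on change is probably small. That is fair, and it is why they are optional here.

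A reader might also infer several stronger things that the documents do not support:

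- **That the list is not stratified by site.** The article is silent on blocking and strata, and such detail is commonly left to the full protocol.
- **That site confounds the treatment comparison.** Site coincides with period, but arm is randomised within both. Imbalance could arise only by chance, which is neither bias nor type I inflation.
- **That interns, supervisors, assessors or season differ by site.** The article does not say so. It presents the consecutive schedule partly as a quality assurance measure.
- **That the Gold Coast needs a new blocked list.** The existing list may already be blocked. Trial status says only that recruitment is ongoing, so whether that site has opened is unknown.

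**Conclusion.** The concern holds as a modest efficiency point. The stated model leaves any site or period difference in change in the residual and, if the list is unblocked, does not correct chance imbalance in site mix. The cost in SE is about 0.1% to 3% for a site effect of 0.1 to 0.5 residual SD with 25% to 50% of participants at the first site. It reaches about 5% when a covariate with partial R² 0.05 is omitted as well. A larger loss needs a site effect well above 0.5 SD, such as 100 ml against an SD of 48 ml, and nothing in the documents supports an effect of that size. Every figure rests on an assumed site effect, site split or partial R². The conclusion that validity is intact does not depend on those values; it follows from randomisation.

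**What to change.** Before unblinding, state the primary model in the analysis plan as outcome on arm + baseline value + site. Age, height and sex may be added if wanted, provided that sex is recorded at baseline and the set is fixed in advance. Draw the bootstrap samples within each arm-by-site cell, so that the standard errors respect the two-site structure and still allow a different error variance in each arm. When the trial is reported, say whether the allocation list was blocked.

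The cost is one line of text and one degree of freedom for site, or four with the optional covariates, out of about 336 participants expected to complete (3 × 112). Age and height are already collected, and the allocation list stays as it is.

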**Methods:**

The study design is a randomised controlled trial of 372 people with no history of respiratory disease between the ages of 50 and 65 years. The cohort will be divided into three equal groups. The first group will receive a simple 10-min treadmill walking program (Ex). The second group will receive joint mobilisation (MB) of the thoracic spine and ribs plus the same walking program (MB + Ex). The third group will receive joint manipulation (MT) of the thoracic spine and ribs plus the same walking program (MT + Ex). All interventions will be administered a total of six times over a 3-week period. The primary outcome measure is lung function: forced expiratory volume in the 1st second and forced vital capacity. The secondary outcome measures include chest wall expansion (tape measurements) and quality of life measurements (36-Item Short Form Health Survey). Outcome measurements will be taken by blinded assessors on four occasions over a 9-week period. Adverse event data will be gathered at the beginning of each intervention session.

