The aims of this trial are to investigate whether manual therapy can mitigate the effects of age-related changes in lung function and whether there is a difference in effect between two different forms of manual therapy.

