## Methods/design

### Study design

The trial is designed as a randomised controlled trial and fulfils the requirements of the Standard Protocol Items: Recommendations for Interventional Trials (SPIRIT) checklist [12] (Additional file 1). The trial will evaluate 372 participants randomly allocated to three equal groups. Participants in Group 1 (Ex), the active control, will undertake a simple exercise program involving a standardised 10-min walking program performed on a treadmill. Participants in Group 2 (MB + Ex) will have manual therapy in the form of joint mobilisation (MB) administered to their thoracic spine and ribs prior to performing the same exercise regime as Group 1. Mobilisation consists of a pre-determined series of manoeuvres (mobilisation protocol) designed to increase joint mobility in the thoracic spine and rib cage (Grade III–IV mobilisation as per Maitland [13]). Participants in Group 3 (MT + Ex) will have manual therapy in the form of joint manipulation (manipulation protocol) administered to their thoracic spine and ribs prior to performing the same exercise regime as Group 1. Manipulation (MT) consists of two separate manipulations (Grade V mobilisation as per Maitland [13]), each involving a high velocity low amplitude (HVLA) thrust directed at the inter-vertebral, costo-vertebral and costo-transverse joints. The first manipulation will be delivered at the level of the upper/middle thoracic spine, while the second will be at the level of the middle/lower thoracic spine. Two different manipulation techniques are available under the trial’s manipulation protocol: supine and sitting. The supine technique, referred to as the ‘Opposite-side thenar/transverse drop’ [14] or ‘Supine wing’ [15] technique, can be delivered with the participant’s thoracic spine in flexion or extension. The sitting technique, referred to as a ‘Long-axis distraction’ [14] or ‘Sitting winglift’ [15] technique, can be delivered using an axilla or elbow hold. The choice of technique will be determined by the treating clinician based on biomechanical factors such as the patient-to-practitioner size ratio. All MT intervention will be administered as non-specific, multi-joint (group) manipulations. Administering MT in this way reduces the total number of manipulations required to address the thoracic spine within a single intervention session, as each manipulation has the potential to affect several thoracic vertebrae and their associated ribs simultaneously. All Ex will be performed immediately after MB and MT intervention, as this has been shown to enhance the synergistic effect of combining the two interventions [9, 16–18]. All intervention sessions will last between 15 and 20 min.

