### Outcome measurements

The primary outcome measure is lung function: FEV_1_ and FVC. The secondary outcome measures include chest wall expansion (tape measurements) and quality of life measurements (36-Item Short Form Health Survey, SF-36). The metric for these measures is mean change from baseline. All outcome measurements will be taken by blinded assessors on four occasions over a 9-week period: at baseline and then at weeks 3, 6 and 9.

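### Two unranked primary outcomes, no primary visit and no primary comparison share one 0.05 threshold, so the false-positive rate for a primary claim exceeds 5%

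*Protocol article*

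**What the plan says.** **Outcomes.** The Outcome measurements section states: "The primary outcome measure is lung function: FEV_1_ and FVC". The Abstract says the same. Neither is placed above the other.

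**Visits.** Measurements are taken "at baseline and then at weeks 3, 6 and 9". The section adds "The metric for these measures is mean change from baseline" and does not say at which visit the change is judged.

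**Arms and aims.** The Study design section has "372 participants randomly allocated to three equal groups": Ex, MB + Ex and MT + Ex. The last paragraph of the Background gives two aims: whether manual therapy helps lung function, and "whether there is a difference in effect between two different forms of manual therapy". Neither is ranked.

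**Test and threshold.** The Statistical analysis section plans a baseline-adjusted ANCOVA for differences between groups, and a p "value of < 0.05 has been set for statistical significance". It gives no order of testing. It then calculates responder proportions for whichever outcomes reach significance, so each outcome is judged on its own.

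**Sample size.** "Sample size calculation was based on change in FVC", at an alpha of 0.05. That section does not call FVC the sole primary outcome, and ties the calculation to no visit and no pair of arms.

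**The concern.** A 5% error rate belongs to one test, or to a set of tests with a rule linking them. Here a positive primary claim could rest on either outcome, at any of three visits, and on an overall or a specific comparison of the arms. Nothing in the article says which result decides the trial, or whether one success is enough.

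The main conclusion is therefore at stake: a favourable result on one outcome at one visit could be presented as a positive primary finding with a false-positive chance well above the nominal level. That cannot be repaired credibly once results are known. The article also describes the trial as fully powered, which has no clear meaning until a primary comparison and visit are fixed.

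**Working it through.** **Inputs from the protocol article.** Two primary outcomes and three post-baseline visits (Outcome measurements); three equal arms (Study design); threshold 0.05 (Statistical analysis). Sidedness is not stated, so two-sided testing is assumed.

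**Inputs assumed.** The document gives no correlations. Those between FEV1 and FVC change, and between visits, were each varied from 0.5 to 0.9.

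**The plan's own figures.** The only error rate given is 0.05, which is right for a single pre-specified test. The sample size of 112 per group does not follow from the printed 200 ml and SD 48 ml: 2 × (1.96 + 0.84)² × (48/200)² ≈ 0.9, so about 1 to 3 per group. That is a separate matter and does not enter the error rates below.

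**Counting the tests under three readings**
- A, mildest: one visit, one overall three-arm test per outcome. 2 × 1 = 2 tests.
- B: the overall test at every visit. 2 × 3 = 6 tests.
- C, fullest: all three pairs of arms, both outcomes, all visits. 2 × 3 × 3 = 18 tests.

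**If tests were independent**, the chance of at least one false positive is 1 − 0.95^k: 9.75% for k = 2, 26.5% for k = 6, 60.3% for k = 18.

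**Allowing for correlation.** The tests share participants, visits and arms, so large-sample results were simulated with no true difference anywhere. Arm means are in standard-error units. A pair is significant if |difference|/√2 > 1.96. The overall test is significant if the sum of squared deviations of the three arm means from their average exceeds 5.99 (the 95% point of chi-square on 2 degrees of freedom).

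| FEV1–FVC / between visits | A: 2 overall tests | B: 6 overall tests | C: 18 pairwise tests |
|---|---|---|---|
| 0.5 / 0.5 | 9.1% | 22.2% | 45.9% |
| 0.5 / 0.9 | 9.2% | 15.2% | 32.7% |
| 0.7 / 0.7 | 8.4% | 18.2% | 37.9% |
| 0.9 / 0.5 | 7.1% | 17.6% | 37.3% |
| 0.9 / 0.9 | 7.1% | 11.9% | 25.9% |

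A repeat run agreed to within 0.1 percentage point at the four corner settings. Intermediate readings lie between: six pairwise tests at one visit give 17–21%, and twelve tests against Ex over all visits give 20–37%. Even one outcome at one visit, with three unadjusted pairs, gives 12%.

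**Checking the remedy.** Suppose FEV1 is tested as soon as the overall FVC test succeeds. Take one arm truly different on FVC, the other two equal, and no effect on FEV1. The null FVC pair and the FEV1 test then each carry a 5% chance of error. Their union would be 1 − 0.95² = 9.75% if independent, and is about 8–9% with FEV1–FVC correlation 0.5–0.9. If FEV1 opens only after every FVC step has succeeded, it can open in this scenario only when the null FVC pair has already been falsely rejected. That adds no new error, and the total stays at 5%.

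**The case against.** **The number of tests is inferred.** This stands. The Statistical analysis section mentions only a difference between groups. It does not list pairwise or visit-by-visit tests, and a 0.05 threshold is compatible with adjusted p values. A reader might infer that the protocol commits to 18 unadjusted tests and a 60% error rate. It does not: 18 is the fullest reading, and 60% requires an independence that cannot hold for two measures from the same spirometry, repeated in the same people, in comparisons that share arms.

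**This is a condensed article, and an analysis plan may exist.** This stands for the multiplicity method, the choice of overall or pairwise tests, and the coding of contrasts. It does not cover the whole point. The article itself names two primary outcomes, fixes the threshold and judges outcomes one by one. Which outcome, visit and comparison decide the trial is the trial's question, not an analysis detail.

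**Both outcomes might be required to succeed.** With one named visit and one overall test each, that rule would hold 5%. But no such rule is stated, no visit is named, and the responder step lets a single outcome succeed alone.

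**Two further inferences go too far.** One is that the planned test cannot address the aims: a three-group ANCOVA can supply both contrasts. The other is that the number needed to treat is explicitly conditional on significance: the condition is attached to the responder proportions, and the sentence on number needed to treat carries none of its own.

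**Conclusion.** The concern holds as a range. With two unranked primary outcomes, no primary visit, no primary comparison and outcomes judged singly at 0.05, the chance of at least one false positive primary result is 7–9%, 12–22% or 26–46%, depending on which of the three readings is followed. The mildest needs a primary visit that the article does not name; every reading that tests all three visits gives at least about 12%. The figures rest on the assumed correlations, two-sided tests, large-sample approximations and no true effect in any arm. The direction does not depend on the exact correlations within the ranges examined. Because this concerns the primary conclusion, it should be settled before unblinding.

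**What to change.** Before unblinding, amend the protocol as follows.

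1. **Name one primary outcome and one primary visit.** Change in FVC at week 3 is a reasoned example: FVC is the sample-size variable and week 3 ends the intervention period. The Background also cites a maximum effect at 3 weeks, but from a study of 20 women that the Discussion calls underpowered and uncontrolled. Another single pre-specified visit would control the error equally well.
2. **Fix the comparisons.** Either test the three arms overall at 0.05 and, only if significant, the three pairs each at 0.05 (a closed procedure for three groups); or test in fixed order the manual therapy arms against Ex, then MT against MB, each at 0.05.
3. **Gate FEV1 fully.** Test it at the same visit, by the same sequence, only if every FVC step has succeeded. Otherwise report it as an estimate.
4. **Report the other visits, chest wall expansion and SF-36** as estimates with confidence intervals.

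**Cost.** No alpha is split and no participants are added. FEV1 and the other visits lose stand-alone primary status, and the strict gate means FEV1 may often be reported only as an estimate. Changing a named primary outcome needs a protocol and registry amendment; the Trial status section says recruitment was still under way at submission.

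The alternative, sharing alpha between the two outcomes (0.05/2 = 0.025 each), keeps both as primary but may cost power. The printed SD of 48 ml would show no loss, but it does not reproduce the stated size. If the SD were 480 ml (an assumption under which an overall three-arm test with evenly spaced means does give 112 per group), power at 112 would fall from 80% to 71%, and 134 per group would be needed.
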